Persons randomized into the standard care services group will receive the usual treatment services available to persons discharged from a CSU. These standard services may include a personalized discharge plan, a follow-up appointment within a month of discharge for evaluation, and connection to other agency services if applicable. A detailed description of standard services can be found in “Intervention description” section. Persons randomized into the mobile and technology-assisted aftercare group will receive standard services plus up to 26 sessions with a community support specialist (CSS) aftercare provider and six months of access to behavioral health mobile applications which are available on demand*.* The CSS is a mental health professional who travels to participants to provide mental health services including counseling, community referrals, motivational interviewing, solution-focused therapy, psychoeducation, and social support, up to once a week for 6 months. Participants randomized to this condition will also receive 24/7 access to evidence-based behavioral health mobile applications that are recommended based on the participant’s diagnostic status, learning style, and goals. The mobile applications are Moodtools-Depression Aid, Virtual Hope Box, Recovery Path, and Intellicare Hub. Each of these applications and the respective types of tools offered within are described in Table 2.

**Table 2 Tab2:** Mobile applications

**Mobile application**	**Resources and tools offered**
Moodtools-depression aid	Psychoeducation Symptom tracking Customized safety plans Cbt activities Journaling activities
Intellicare hub	Psychoeducation Symptom tracking Goal setting Relaxation techniques Positive thinking activities
Virtual hope box	Coping skills Relaxation techniques Positive thinking activities
Recovery path	Psychoeducation Goal setting Coping skills Trigger management Referrals to recovery meetings Daily check-ins

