#### Intervention description

The mobile and technology-assisted intervention is designed as an aftercare program for persons released from a CSU and addresses treatment retention barriers by combining in-person assistance and technology-aided tools. The aftercare program will be delivered to participants by Community Support Specialists (CSSs) who are employees of our partnering behavioral health agency and trained in the research study protocol. The aftercare program will be delivered up to once a week for 6 months or 26 sessions; the needs of each participant determine the frequency of sessions.

The mobile and technology-assisted aftercare program services will include the CSSs providing in-person assistance by meeting with participants at their homes or nearby public settings and providing participants with 24/7 access to behavioral health services through mobile applications. During sessions, the CSSs will provide various assistance, including social support, psychoeducation on behavioral health, and health management skills, and assist with the navigation of community resources, including housing, meeting basic needs, and other tangible supports that promote community stability. To provide support in-between session work, the CSSs will give guidance on using the mobile apps that are relevant to the participant. Additionally, CSSs will employ motivational interviewing and solution-focused brief therapy techniques in the sessions. The mobility of the aftercare program differs from standard services in which persons are expected to return to the behavioral health agency approximately 1 month after discharge from the CSU. The mobile and technology-assisted aftercare program is based on the Community Health Model (CHW) wherein mobile CHW solutions provide resources, counseling, education, and assistance to vulnerable and disadvantaged populations [29, 30]. Similar to CHW programs, a vital component of the CSS work is augmenting interventions at our partner mental health agency by providing community-based services and mobile app support to address client barriers to treatment directly.

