Mobile applications incorporated into this intervention include Moodtools-Depression Aid, Virtual Hope Box, Recovery Path, and Intellicare Hub. All mobile-based applications have undergone thorough investigation in one or a combination of RCTs/clinical trials, were developed with mental health professionals, and have shown a positive impact on intended outcomes [31–36]. Participants will not be required to use the mobile applications. However, the participants will be encouraged to use the apps by the CSS. The CSS will incorporate dialogue and instruction on the utilization of the apps into the intervention sessions. Specifically, during sessions, the CSS will ask participants about their use of the apps, what they like and do not like, and provide information on how the app(s) may assist the participant in reaching their goals. The CSS will not record, track, or obtain any data from the mobile apps on the participant’s phones. If participants do not wish to use the apps, they will not have to. The research team will not track, record, or obtain any data from the apps on the participant’s phones. The research team will collect data on the use of the apps through an open-ended question measure, Qualitative Technology Use, described in “Measures” section. The above mobile applications were chosen for a variety of reasons, including their development standards, accessibility for download, and range of mental health and substance use-related tools and resources that are promising and apply to our intervention and population.

Standard care for persons discharging the CSU will include a personalized discharge plan and a follow-up appointment with the agency within a month for evaluation and continued mental health services. At the follow-up appointment, participants may be connected to other agency services. These services include outpatient counseling for behavioral and emotional problems, psychiatric services, group therapy, case management, rehabilitation services, homeless recovery services, employment services, medication-assisted treatment, group-based team-building activities, a primary care clinic, and forensic services. Individuals may also receive referrals for applicable healthcare services, access to residential and outpatient substance abuse treatment services, and access to a tablet.

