#### Measures

Measures for the Mobile and Technology-Assisted Aftercare Group and Standard Services Group include administrative records and direct data collection from participants. The primary outcomes for this feasibility study are participant recruitment, participant retention, feasibility, and the acceptability of the intervention. Participant recruitment will be measured by the number of eligible participants who consent to participate out of the total number of eligible participants. Participant retention will be measured by the proportion of the intervention completed by participants. Feasibility and accessibility will be assessed by triangulating the qualitative and quantitative data from study participants—the CSU professionals and patients.

 The secondary outcomes include individual stabilization and well-being, frequency of both acute and long-term treatment use, re-admission to a crisis stabilization unit, and arrest rates or re-encounters with law enforcement. The secondary outcomes will be assessed to find trends that will inform the future RCT. We will examine the feasibility of collecting the data, the sensitivity of the measures, estimates for effect size and sample size, and other factors that may impact the ability to detect outcomes. For the pilot study, the secondary outcomes are not meant to measure impact; instead, they are intended to examine trends in outcomes to inform the design of the intervention and study protocol for the future RCT. Secondary outcomes will be measured using screening questions, demographical information, clinical assessment tools, and baseline and follow-up interviews with each participant. Administrative data from the CSUs and law enforcement will be collected on client characteristics, including demographics (e.g., race, gender, age, county of residence), criminal history (e.g., current reason for law enforcement contact, prior arrests, and reasons for arrest, and prior CSU stays), and behavioral health status (e.g., diagnoses, prior and current treatment utilization, and medication-assisted treatment). Table 3 shows the measures related to each secondary outcome described below.

**Table 3 Tab3:** Primary and secondary measures

**Primary outcomes**	**Measures**
Participant retention	Number of recruited participants who complete the intervention
Participant recruitment	Number of eligible participants who agree to participate out of the total number of eligible participants

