Feasibility of intervention	Number of intervention sessions completed by each participant
Acceptability of intervention	Qualitative interviews with CSU stakeholders
**Secondary outcomes**	**Measures**
Individual stabilization and well-being	Brief Symptom Inventory Brief COPE Hearth Hope Index Trauma History Questionnaire Financial security Education and employment Education employment aspiration and satisfaction Network composition survey
Acute and long-term treatment use	Service assessment for children/adults California Psychotherapy Alliance Scale Qualitative CSU experience Qualitative technology use
Admission into CSU	Administrative data of re-admission into CSU
Arrest rates/re-encounters with law enforcement	Administrative data of arrest rates Lawbreaking Police-community interaction survey

The Brief Symptom Inventory [38] is a 53-item assessment covering nine dimensions through subscales: somatization, obsession-compulsion, interpersonal sensitivity, depression, anxiety, hostility, phobic anxiety, paranoid ideation, and psychoticism. Scores for each subscale range from 0 to 4, with higher scores meaning more symptoms reported. Reported internal consistency reliability ranged from *⍺*=0.75 to 0.89 [39], test-retest reliabilities ranged from 0.68 to 0.91, acceptable convergent validity, and construct validity [40].

The Brief COPE [41] assessment is a 28-item index that assesses coping self-efficacy and confidence coping with stress using an intensity scale of 1 to 4. The higher the score, the greater the coping self-efficacy. The Brief COPE has been found to have acceptable reliability *⍺*=0.81 [42].

The Herth Hope Index [43] is a 12-item measurement tool that assesses hope, self-efficacy, and the respondent’s outlook on life. The tool uses an intensity scale from 1 to 4, where the higher reported scores indicate a higher level of hope. The Herth Hope Index has been used in 10 countries and has shown acceptable reliability and acceptability across 13 studies [44].

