### Aim 3 study design

#### Aim 3: Design a multi-site RCT to compare the relative impact of CSUs with mobile and technology-assisted aftercare to CSUs without mobile and technology-assisted aftercare

The goal of Aim 3 is to design a large-scale multi-site RCT to compare CSUs with and without mobile technology-assisted aftercare on short and long-term outcomes. It is anticipated that the outcomes in this future RCT will include individual stabilization post-crisis, arrest rates, use of acute services, and increased engagement with long-term treatment

To reach Aim 3, the qualitative data from CSU stakeholders in Aim 1, and data from the pilot trial of the CSU aftercare intervention in Aim 2, will be synthesized to inform and develop a study protocol for the future large-scale RCT. Following the guidelines from the CONSORT extension to pilot trials, data from Aims 1 and 2 will be used to inform the feasibility and suggest critical areas where further development or modification may be required [58]. For instance, data from Aim 1 will explore barriers and facilitators to intervention implementation for agencies and the perceived acceptability of the intervention for our target population and stakeholder procedures. Analysis of Aim 2 data will inform sample size details, referral, appropriate randomization procedures, retention and attrition challenges, and whether randomizing to follow-up mobile supports is the correct variable to randomize on or if there is another more appropriate randomizing variable. Prespecified progression criteria will be assessed from our pilot study to determine whether to proceed with the development of the future RCT. Our progression criteria include the following: (1) do the results of the pilot study suggest positive effects on the treatment group?; (2) did feedback from participants and stakeholders demonstrate the feasibility and acceptability of the intervention?; (3) can a future RCT feasibly be implemented?; and (4) are there potential future partners for a future RCT?

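### The primary retention outcome is defined in two conflicting ways, both describing adherence in the treatment arm only, so as defined it does not give retention in the trial by arm

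*Protocol article*

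**What the plan says.** The Measures section for Aim 2 lists participant retention among four primary outcomes. The text reads: "Participant retention will be measured by the proportion of the intervention completed by participants". Table 3 in the same section gives the measure as "Number of recruited participants who complete the intervention". Table 3 then measures feasibility of the intervention by a closely related quantity: "Number of intervention sessions completed by each participant".

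The Intervention description says: "The aftercare program will be delivered up to once a week for 6 months or 26 sessions", and adds that "the needs of each participant determine the frequency of sessions". On the technology component it says: "Participants will not be required to use the mobile applications". On the comparator, the Aim 2 study design says: "Persons randomized into the standard care services group will receive the usual treatment services available to persons discharged from a CSU".

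Two places say what retention is for. The Aim 2 Sample section says that recruitment feasibility and retention trends will bear on the sample size chosen for the subsequent RCT. The Aim 3 study design says: "Analysis of Aim 2 data will inform sample size details, referral, appropriate randomization procedures, retention and attrition challenges".

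The Aim 2 Data collection section schedules a baseline interview, then T1 (2 weeks), T2 (3 months) and T3 (6 months), in both groups. Completing these interviews is not named as the retention outcome.

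**The concern.** Two kinds of retention are mixed. Staying in the aftercare programme is adherence and exists only for those offered the programme. Staying in the trial means still providing outcome data, and it exists for everyone randomised. The purpose given in the Sample and Aim 3 sections calls for the second, while both definitions describe the first.

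This matters because the planned RCT must be inflated for missing outcome data, and the designers need to know whether the loss differs by arm. A difference is plausible here. Treated participants may be visited as often as weekly and may have a phone paid for by the study, whereas standard care centres on one follow-up appointment within about a month. A retention outcome confined to the treated arm cannot show such a difference.

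The two definitions also do not agree with each other, so two analysts following the article could report different figures for one primary outcome.

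**Working it through.** The article states no retention rate, assumed dropout or power, so there is no retention figure to reproduce. The sample size is internally consistent: 3 counties × 8 = 24 = 12 + 12. The rest sets the definitions against the design. All rates and session counts below are assumptions for illustration.

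**1. Text against Table 3.** The text yields a fraction of the programme, per person or averaged. Table 3 yields a number of people. Neither produces a value for a control, who has no study intervention to complete. Table 3 speaks of recruited participants, which covers both arms, so even its base is open:

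| Completers among 12 treated | Out of 24 recruited | Out of 12 treated |
|---|---|---|
| 12 | 12/24 = 50% | 12/12 = 100% |
| 9 | 9/24 = 37.5% | 9/12 = 75% |

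**2. Denominator for the proportion.** The article gives 26 sessions as a maximum and lets need set the frequency. It fixes neither 26 nor any individual plan as the denominator. The spread between those two readings is:

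| Sessions needed and attended | Against the ceiling | Against need |
|---|---|---|
| 13 | 13/26 = 50% | 13/13 = 100% |
| 6 | 6/26 = 23.1% | 6/6 = 100% |

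This shows how far the reported value depends on an unstated choice. It does not predict what would be reported. App use is optional, so it supplies no completion standard either.

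**3. Adherence is not trial retention.** A treated participant who stops sessions early but gives the T3 interview is retained in the trial and not in the programme. One who attends many sessions but misses T3 is the reverse. Neither stated measure therefore yields the attrition fraction d.

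**4. What the RCT needs.** Enrolment = N/(1 − d), with N the number needed with outcome data. For N = 100:

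| d | Enrol |
|---|---|
| 20% | 100/0.80 = 125 |
| 30% | 100/0.70 = 143 |
| 40% | 100/0.60 = 167 |
| 50% | 100/0.50 = 200 |

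**5. What completion of the T3 interview would give.** Exact (Clopper–Pearson) 95% intervals:

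| T3 completed | Rate | 95% CI |
|---|---|---|
| 12/24 overall | 50.0% | 29.1% to 70.9% |
| 16/24 overall | 66.7% | 44.7% to 84.4% |
| 18/24 overall | 75.0% | 53.3% to 90.2% |
| 20/24 overall | 83.3% | 62.6% to 95.3% |
| 9/12 in one arm | 75.0% | 42.8% to 94.5% |

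For the 18/24 case, enrolment per 100 evaluable runs from 100/0.902 = 111 to 100/0.533 = 188. For 9/12 in one arm it runs from 100/0.945 = 106 to 100/0.428 = 234. The estimate will be rough even when defined properly, but it will be an estimate of the right quantity.

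**The case against.** The strongest objection is that nothing is lost. Interviews at T1 to T3 are scheduled in both arms, the Aim 3 section says Aim 2 data will inform attrition, and the Measures section says the feasibility of collecting the secondary outcome data will be examined. A reader might infer from the definitions that the pilot cannot give an attrition rate, or that differential attrition cannot be estimated. The documents do not support that, because both can be counted from data already planned. What stands is narrower: the outcome named as retention does not give these quantities, and no other named outcome does.

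Second, retention in treatment is a legitimate construct here. The introduction frames the problem as keeping people in treatment after discharge, and the partner agency's administrative data will record engagement and retention in acute and long-term treatment. That supports reporting adherence, but not letting it stand for trial retention when sample size is the stated use.

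Third, the programme lasts 6 months, so reaching 6 months is a plausible reading of completing it, and the full protocol or implementation guide may define completion. This is fair. It does not reconcile the text with Table 3, both of which are shown, and it does not extend either measure to controls.

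Two further inferences should be resisted. One is that a participant with modest needs would be scored as poorly retained, for example 8/26 = 31%; that assumes a denominator the article never fixes. The other is that setting the 9/12 interval beside the 18/24 interval measures the harm. The first would be programme completion in one arm and the second follow-up pooled over two, at an assumed rate, and per-arm reporting has the 12-person width in any case.

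The overlap with the feasibility measure is also partial. Table 3 counts sessions per participant for feasibility and people for retention, and the text assesses feasibility by combining qualitative and quantitative data.

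**Conclusion.** The point holds in limited form. A primary outcome has two definitions that disagree. Both apply only to the 12 treated participants, and neither has a stated completion point. As defined, it measures adherence in one arm and cannot supply retention in the trial by arm, which is the quantity needed for the use the Sample and Aim 3 sections describe. Those sections say retention will inform the RCT's size; they do not say it will determine it.

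The ambiguity can be large: the same 12 completers read as 50% or 100%, and the same 13 sessions as 50% or 100%. These figures rest on assumed counts and show how far the readings can differ, not an expected error. Because the interviews are already planned in both arms, the defect lies in the definition and not in data collection. It should be fixed before analysis but does not threaten the pilot.

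**What to change.** 1. Define participant retention as the proportion of all randomised participants, per arm and overall, who complete the T3 (6-month) interview. Report T1 and T2 completion in the same way, with exact 95% confidence intervals.
2. Report intervention adherence separately, in the treatment arm only: sessions attended, as a count and out of sessions scheduled, together with whether the participant is still in contact with the community support specialist at 6 months. The contact item is needed because attended over scheduled can look high for someone who disengages and has nothing further scheduled.
3. Use the same wording in the Measures text and Table 3.

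The interviews are already scheduled in both arms, so the cost is rewording plus a log of scheduled sessions and of contact at 6 months. With 24 participants the intervals will be wide, and the RCT planning should carry that uncertainty forward instead of relying on the point estimate.

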The research team developed the qualitative CSU questionnaire to explore the respondent’s experience while detained and receiving services within a CSU. The qualitative CSU experience questions are designed to assess the participant’s perceived helpfulness and impact from the CSU services which may affect the degree of stabilization respondents feel after discharge from the CSU. The Qualitative CSU experience is a five-item qualitative questionnaire. Qualitative CSU experience is a short survey containing both yes/no and open-ended qualitative questions. The questionnaire asks about the history of admission into CSUs, services received while at CSUs, and several questions regarding the participant’s opinion of their CSU stabilization experience. These opinion questions include what was helpful during their stay, what was not beneficial, and what they would like to change about the program.

The research team developed the Qualitative Technology Use questionnaire to capture the respondents’ opinion on and use of the behavioral health mobile applications. The Qualitative Technology Use is a short four-item survey and contains qualitative and quantitative questions. The questions are designed to address the feasibility and acceptability of the incorporation of mobile applications into our intervention. To do so, questions assess the frequency of use and what participants like and do not like about each app they use. Both treatment and control participants will be asked if they currently use mobile applications to assist with mental, behavioral, or substance use symptoms/treatment. Treatment group participants will be asked if they use any of the recommended apps or any other mobile apps they may use for behavioral health, mental health, and substance use assistance.

Our partnering mental health agency will collect administrative data to record any points of contact or engagement with participants. Administrative data will include re-admissions into CSUs, CSU admission and discharge criteria, number of contact attempts by the mental health agency, type and number of services offered to the participant, and engagement in and retention in acute and long-term treatment by the participant.

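### Table 3 measures feasibility by a count of completed sessions, but need sets how many are planned, so the count alone cannot separate full from poor delivery.

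*Protocol article*

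**What the plan says.** The Measures section of Aim 2 states: "The primary outcomes for this feasibility study are participant recruitment, participant retention, feasibility, and the acceptability of the intervention". In Table 3 the feasibility row is measured by "Number of intervention sessions completed by each participant", with no denominator. The recruitment row of the same table does have one, the number of eligible people.

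The amount of intervention is given as a maximum. The Aim 2 study design describes "standard services plus up to 26 sessions with a community support specialist (CSS) aftercare provider". The Intervention description says "up to once a week for 6 months or 26 sessions" and continues that "the needs of each participant determine the frequency of sessions". The article gives no minimum and does not say that a planned number of sessions is recorded for each participant.

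Three other statements bear on the point:

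- The text before Table 3 says: "Feasibility and accessibility will be assessed by triangulating the qualitative and quantitative data from study participants".
- The same paragraph says of a different primary outcome: "Participant retention will be measured by the proportion of the intervention completed by participants". It does not say how many sessions make up the whole intervention. Table 3 instead measures retention as a count of completers, without defining completion.
- The agency's administrative data are to include "number of contact attempts by the mental health agency, type and number of services offered to the participant".

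**The concern.** When the intended dose differs between participants, a count of completed sessions has no fixed meaning. A participant who needed little contact and received all of it can have the same low count as one who needed weekly contact and could not be found. Only the second is a delivery problem. It is a realistic one, because the Sample section itself describes the population as vulnerable and highly transient.

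The pilot exists largely to learn whether this aftercare can be delivered. The Discussion makes development of a large trial depend on the pilot showing feasibility and acceptability, and the Aim 2 analysis strategy intends to look at differences by county. With 12 intervention participants over three counties, the average is 12/3 = 4 per county. A few low-need participants could make delivery in one county look weak when every planned session was held.

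**Working it through.** **Inputs from the article.** Ceiling: 26 sessions, up to weekly for 6 months (Aim 2 study design; Intervention description). Frequency: set by need (Intervention description). Intervention arm: 12 participants (Sample). Measure: completed sessions per participant (Table 3).

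**Reproducing the ceiling.** Weeks in 6 months = 365.25 / 2 / 7 = 26.09, so weekly contact gives 26 sessions. The article's figure is right.

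**Assumed plans.** The article gives no individual plans. For illustration: weekly = 26; fortnightly = 26/2 = 13; monthly = 6.

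**Same count, different plans.** Delivery = completed / planned.

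| Completed | Weekly plan (26) | Fortnightly plan (13) | Monthly plan (6) |
|---|---|---|---|
| 6 | 6/26 = 23% | 6/13 = 46% | 6/6 = 100% |
| 13 | 13/26 = 50% | 13/13 = 100% | above plan |

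**Does dividing by the ceiling help?** No. Against 26, a count of 6 is always 23% and a count of 13 always 50%, even where the whole needs-based plan was delivered.

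**The same ambiguity in a group mean** (again with assumed plans and delivery rates). If half the participants are planned weekly, half monthly, and 90% of sessions are held, the mean is 0.5 × 26 × 0.9 + 0.5 × 6 × 0.9 = 11.7 + 2.7 = 14.4. If all are planned weekly and 55% are held, the mean is 26 × 0.55 = 14.3. The means are almost equal although delivery is 90% in one case and 55% in the other.

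**Could a ratio mislead too?** Yes, if the plan is rewritten after failure. A participant on a weekly plan who is reached 6 times scores 6/26 = 23%. If missed visits led staff to reset the whole plan to monthly, the score would become 6/6 = 100%. The denominator therefore has to be fixed in advance and protected from such reductions.

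**The case against.** The strongest reply is that the count does not stand alone. The Measures text combines interview and numerical data when judging feasibility. The Qualitative Technology Use questions address feasibility of the apps. The analysis strategy gives both kinds of data equal weight and uses the qualitative data to explain quantitative trends. A low count would be read beside interviews and agency contact records. This stands in part: a reader might infer from Table 3 that feasibility rests on the count alone, and the text does not support that. But none of these sources defines how many sessions were intended, and the article does not commit to recording why a session was not held. Fidelity monitoring observes one session a week, so it does not measure sessions that failed to happen.

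A second reply is that a proportion already appears among the primary outcomes, under retention. That is a separate outcome whose whole is undefined, and Table 3 gives a different measure for it.

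A third is that the raw count shows the dose actually delivered, which is useful in designing the later trial, and that a ratio of held to scheduled sessions flatters delivery when hard-to-reach participants have few sessions scheduled. Both parts are right. They are reasons to keep the count and to guard the denominator, not to do without one.

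A last reply is that tabulation belongs in the full protocol or analysis plan. That would answer an omission. Here the article itself states the measure, and the measure does not suit a dose that varies by need.

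**Conclusion.** The point holds as a weakness in how a primary feasibility outcome is measured. The count alone cannot separate a fully delivered low-need plan from a poorly delivered high-need one. Under the assumed plans, 6 sessions can be anything from 23% to 100% of what was intended. The true spread depends on how far plans differ in practice; if nearly everyone were planned weekly, the problem would be small.

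Two stronger readings are not supported. A reader might infer that the pilot could declare a deliverable program infeasible, or the reverse. The progression criteria, given in the Introduction and under Aim 3, contain no session threshold, and the criterion that names feasibility of the intervention turns on feedback from participants and stakeholders. A reader might also infer that the missing denominator is already held in the administrative data. The article lists contact attempts and services offered, but not planned sessions or reasons for missed ones, and contact attempts are not planned sessions.

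**What to change.** Change the feasibility row of Table 3 as follows:

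1. Record prospectively the session frequency agreed for each intervention participant, with the date of and reason for every later change.
2. Report sessions completed divided by sessions planned, per participant, beside the raw count.
3. Code each planned session that was not held as reduced by agreed need, declined, not reached, or specialist unavailable.
4. State that a reduction in frequency following missed contact does not lower the denominator.

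The cost is small but not nil: a planned-session field and a reason code added to the agency record for 12 participants. Frequency remains set by need exactly as now, and the session schedule is unchanged.
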